The estimation of Cohen's d is required, with the formula Cohen's d = (δ(Δ) / SDestimate). Referencing studies in similar populations [<https://www.ncbi.nlm.nih.gov/pmc/articles/PMC8939409/>], SDestimate is taken as 250. Therefore, the relevant command is pwr.t.test (d = cohen_d, sig.level = 0.05, power = 0.80, type = "paired", alternative = "two.sided"), resulting in a sample size estimate of 34. Thus, the estimated sample size for the experimental group should be no less than 34 individuals; considering a natural dropout rate of 20%, the sample size for the experimental group should be at least 41 individuals. A ratio of 2:1 will be used to include 20 recreational gamers in the intervention group. A total of 61 participants are required for the intervention group. In order to maintain appropriate comparability, we will recruit an additional 61 participants with matching demographic profiles and equivalent levels of IGD (Internet Gaming Disorder) severity for the control group. Thus, the study demands a cumulative participation of 122 individuals in total.

1. ***Methods of randomization and concealed allocation. [Randomization is used to reduce the risk of selection bias. Methods for generating random number sequences include computer software, random number tables, semi-random or pseudo-random methods (such as using dates, birthdays, or even/odd numbers of hospital visits). Please describe the individuals involved in generating random number sequences and the methods they use. Concealed allocation is used in treatment studies to reduce the risk of selection bias. Key steps in concealed allocation include having a designated person determine the allocation sequence, ensuring that this person is not involved in enrolling participants, and securely storing the allocation table. Please provide detailed descriptions of these steps. Central randomization is a robust method of concealed allocation. Describe the individuals and methods involved in determining the allocation sequence]***

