(1) In this study, the intervention period focused on breath meditation lasts for one week and serves as a concise mindfulness behavior training. The study will involve a baseline collection of EEG and other relevant data for all participants, a one-week training on the intervention content, collection of post-intervention EEG and other relevant data, and follow-ups (one week, one month, four months, six months, and one year after data collection post-intervention). During the follow-up phase, participants will undergo multiple mindfulness training sessions. Grouping will occur after the baseline data collection for participants is completed.

(2) The breath meditation training is the primary intervention method employed in this study. The design includes grouping into an experimental group and a control group: the experimental group (breath meditation training) and the control group (relaxation training). The recruited participants are from the same school, and their connections make it challenging to implement the criteria for double-blind randomization.

(3) The randomization process for this trial will utilize the random sequence generator available at random.org.

1. ***Blinding. [Blinding is used in treatment studies and diagnostic trials to reduce the risk of implementation bias and measurement bias. Implementing strict confidentiality measures, such as using placebos or simulating procedures, is an effective blinding method. If blinding is necessary and feasible for your study, describe the methods and procedures for implementing blinding]***

This trial involves group therapy, with participants being students from the same school. Therefore, it is possible that among participants who may know each other or even among those who do not, conversations related to the experimental training they are undergoing may arise. Additionally, maintaining blinding for the researchers is quite challenging, as they can easily be influenced by information related to the experiment during the process. As a result, it is not feasible to meet the double-blind requirements of clinical trials.

1. ***Outcome Measures. [Outcome measures are used to evaluate the results of a study and can include primary, secondary, and safety measures, including adverse events and reactions. Please describe the names of the measures, the methods of measurement, and the time points at which they are assessed]***

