(5) Participant Termination: To ensure the health of the participants, any adverse events will constitute a termination condition. Researchers will discuss such situations with the affected participants to consider premature termination of their intervention. Appropriate clinical interventions will be provided to them with their consent.

(6) Participant Suspension: In this trial, we will allow participants to request suspension of their involvement in the intervention. If any requests for suspension are made, participants will be moved to a future intervention group after the trial team assesses that no adverse events or reactions have occurred. Data collected from these participants during the current trial will not be included in the final data analysis.

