| --- | --- | --- | --- | --- | --- | --- | --- | --- | --- | --- | --- | --- | --- | --- | --- | --- | --- | --- | --- | --- | --- | --- | --- | --- | --- | --- | --- | --- | --- | --- | --- | --- | --- | --- | --- | --- | --- | --- | --- | --- |

1. ***Definition, identification methods, and management systems for adverse events and reactions.***

[name] [[25](#_ENREF_25" \o "Farias, 2020 #701)] systematically describes the adverse events and reactions caused by meditation (meditation adverse events, MAEs) in the text, which we categorize as follows:

**Mental MAEs:** The most common include anxiety and depression, while other relatively common issues include psychotic or delusional symptoms, dissociation or depersonalization, fear or phobia, trauma re-experiencing, and suicidal thoughts and behaviors.

**Physical MAEs:** The most common is bodily tension, followed by pain and gastrointestinal issues. Localized pain often involves the abdomen/stomach and neck. Most physical MAEs are based on patient self-reports; however, some variables also used physiological and biological measurement methods, such as heart rate, blood pressure, skin conductance, and cortisol levels (it is not possible to rule out that these physiological measuring methods might cause side effects).

**Neurological/Cognitive MAEs:** The most common are abnormal cognitive experiences, including thought disorganization, forgetfulness, sensory hypersensitivity, and impaired memory reliability. Some patients also experienced involuntary bodily movements and muscle contractions during meditation.

Based on the types of adverse effects mentioned above, to address adverse events during the intervention process, we have included relevant adverse reaction feedback questions in the weekly follow-up questionnaires. The experimental group will conduct weekly monitoring; after collecting the questionnaires, if an adverse event feedback option is marked "yes," the relevant person in charge from the medical school and psychology department will be responsible for communicating with the subjects, assessing their psychological and physiological conditions, and gauging the subjects' willingness. After a tripartite consensus (medical school, psychology department, and the individual subject), they will decide whether the subjects experiencing adverse events can participate in subsequent research.

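### Weekly adverse-event monitoring, and the review that follows a 'yes', are stated for the breath meditation group and not for relaxation

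*Protocol*

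**What the plan says.** The relevant text is in the protocol section headed Definition, identification methods, and management systems for adverse events and reactions. After listing mental, physical and neurological or cognitive adverse events of meditation, it explains that "to address adverse events during the intervention process, we have included relevant adverse reaction feedback questions in the weekly follow-up questionnaires". That sentence names no arm.

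The next sentence begins "The experimental group will conduct weekly monitoring". It continues, without a break, to what happens when a form comes back with a 'yes': the responsible people in the medical school and psychology department contact and assess the participant. The decision on further participation then comes "After a tripartite consensus (medical school, psychology department, and the individual subject").

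The section Methods of randomization and concealed allocation, item (2), names the two groups: "the experimental group (breath meditation training) and the control group (relaxation training"). The adverse-events section does not mention the control or relaxation group.

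**The concern.** Taken at its word, the sentence gives one arm a weekly adverse-event check and a structured continuation review that the other arm is not promised. Three features make this worth tidying.

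- **The listed events are not specific to meditation.** Anxiety, depression, bodily tension, pain and forgetfulness can all occur without training. Entry requires PHQ-9 below 20 and GAD-7 below 11, so scores up to 19 and 10 are allowed and some symptoms may be present at baseline in either arm. An additional prompt in one arm could pick up more of this background there.
- **Detection has consequences.** Under Participant Termination, "any adverse events will constitute a termination condition", after which early termination is discussed with the participant. The review after a 'yes' also decides on continued participation. Unequal prompting could therefore bear on who continues as well as on what is counted.
- **The trial is not blinded.** The Blinding section says double-blinding is not feasible. Asking both arms the same questions at the same times is one of the simple safeguards left.

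**Working it through.** The protocol gives no figure on this point and no calculation decides it. The check was to compare every use of the key term and every safety provision.

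**1. Who is the experimental group?**

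- Randomisation section, item (2): the breath meditation arm, set against relaxation.
- Sample size section: "the estimated sample size for the experimental group should be no less than 34 individuals", raised to 41 for dropout. These are the participants with internet gaming disorder. Adding 20 recreational gamers gives 41 + 20 = 61, which that section calls the intervention group. A further 61 form the control group (61 + 61 = 122).
- The term is therefore not used uniformly: once it is the whole breath meditation arm, once only the 41 within it. In both places it means participants allocated to breath meditation. In neither does it mean staff or include relaxation.

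**2. What are staff called?** Mostly researchers. Also the research team (EEG adverse-reaction paragraph), the trial team (Participant Suspension: "after the trial team assesses that no adverse events or reactions have occurred") and, in the Participant management system, a contact group made up of researchers. Outside the disputed sentence they are never called the experimental group.

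**3. Which safety provisions apply to whom?**

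| Provision | Section | Arm named |
| --- | --- | --- |
| Daily inquiry during the intervention period | Outcome Measures, (3) | None; participants generally |
| Termination after any adverse event | Participant Termination, (5) | None |
| Stopping EEG on an adverse reaction | Adverse-events section, EEG paragraph | None |
| Emergency team, throughout the study | Participant management system, (2) | None |
| Questions in the weekly questionnaires | Adverse-events section | None |
| Weekly monitoring | Adverse-events section | Experimental group |
| Review after a 'yes' | Adverse-events section | By position only: same sentence as the monitoring |

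Only the last two rows carry, or inherit, an arm restriction. No other section extends them to relaxation. The Fig 2 schedule and Table 1 list neither a weekly questionnaire nor an adverse-event item, so they do not resolve it.

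**4. How long does the weekly form run?** The questions are tied to the intervention process. The randomisation section, item (1), gives the intervention as one week, but adds that "During the follow-up phase, participants will undergo multiple mindfulness training sessions". The Fig 3 caption, by contrast, says the control group has no further practice after training. Two cases follow.

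- *Forms confined to the one-week intervention.* There is one weekly form per person, in a week when everyone is also asked daily, so any added ascertainment is probably small. If relaxation participants are not already receiving the form, including them adds 61 × 1 = 61 forms. If they are, it adds none.
- *Forms continue into follow-up.* The daily inquiry is stated only for the intervention period, so it may no longer offset a difference. The number of forms cannot be derived because no end date is given.

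No event rate or reporting probability is given, so the effect on event counts cannot be calculated in either case.

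**The case against.** The strongest reply is that the sentence describes work done by staff. Participants do not conduct monitoring or collect questionnaires, so the phrase may be a loose translation of the team running the trial, in which case both arms are covered. That is possible and cannot be excluded. But the protocol defines the phrase as a trial arm and uses it elsewhere only for participants. If it is a slip, the sentence still needs the same correction.

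A second reply is that the questionnaires, and the subjects reviewed, carry no arm label. This stands. A reader might infer that the breath meditation arm completes 61 forms and relaxation none. The documents do not support that: only the monitoring is tied to a group, and the forms may already go to both.

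A third is that the declared safety indicator, the daily inquiry, applies to all participants. This also stands. It rules out the inference that relaxation participants go without safety monitoring, and the broader one that event counts by arm cannot be compared at all. It does not give relaxation the weekly monitoring or its review.

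Finally, closer watching may be deliberate. The listed events are those of meditation, and the Fig 3 caption has the control group stopping practice after training. That would be a reasonable safety choice, but the protocol does not say that it was made.

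**Conclusion.** The point holds in a limited form. As written, weekly adverse-event monitoring is assigned to breath meditation, the review after a 'yes' follows it by its place in the sentence, and neither is stated for relaxation. The possible asymmetry goes no further than those two items.

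This rests on reading the experimental group as the protocol defines it. How much it matters depends on whether the forms outlast the daily inquiry, which is not stated. The wording problem is clear; whether the arms would in practice be treated differently is uncertain.

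A reader might go on to infer bias in the efficacy comparison. The documents do not support this: no between-arm test of adverse events is stated, termination is discussed rather than automatic, and the daily inquiry could bring the same events to light in either arm. The point is a low-cost improvement to the safety data.

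**What to change.** Replace the monitoring sentence with: *Participants in both the breath meditation and relaxation groups will complete the same adverse-event questions at the same times, and a 'yes' in either group triggers the same review.* State when the weekly questionnaire starts and ends, and report adverse events by arm.

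If closer watching of breath meditation alone is intended for safety, say so and base any between-arm comparison of adverse events on the daily inquiry only.

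The cost is one protocol sentence and at most a few short extra forms per relaxation participant: one each if the form covers only the one-week intervention, and none if those participants already receive it. Reviews of any additional 'yes' answers would follow the procedure already described.

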(1) Primary indicators: average daily gaming time (self-reported by participants), Five Facet Mindfulness Questionnaire (FFMQ), Internet Addiction Test (IAT), Game Craving Scale (adapted from QSU-Brief), Adolescent Executive Functioning Scale (EFS-A), Barratt Impulsiveness Scale, State Mindfulness Scale, Game Craving Visual Analogue Scale, behavioral data, and EEG data (from EEG equipment).

(2) Secondary indicators: Self-Rated Sleep Status Scale, Depression-Anxiety-Stress Scale (DASS-21), Positive and Negative Affect Schedule (PANAS).

(3) Safety indicators: Researchers will inquire daily during the intervention period whether participants experience any adverse reactions. If there are any adverse reactions, they will communicate in person or by phone with the research staff.

Measurement time points are detailed in item 5.

1. ***Definition of Participant Effectiveness Determination. [This includes definitions for participant withdrawal, exclusion, loss to follow-up, confounding factors, study discontinuation, and study suspension]***

(1) Participant Withdrawal: Each participant can withdraw from the study at any time during the experiment without providing any reason. Participants who withdraw voluntarily will not be included in the analysis. Under the conditions of a mixed study, we have a complete access procedure for withdrawn participants. If participants are willing to provide a reason for their withdrawal, it will be recorded by the researchers.

(2) Participant Exclusion: If participants cannot consistently participate in the group interventions during the training process—where the focused breathing meditation training lasts one week—those who attend fewer than 5 sessions will be considered not fully intervened and should theoretically be excluded or adjusted using a mixed-effects model.

(3) Participant Loss to Follow-up: If any participant cannot be contacted for two consecutive attempts after the intervention is completed, they will be classified as lost to follow-up.

(4) Participant Contamination: After the intervention is completed, we will conduct a census of participants. If any participant in the control group attempts to learn about the training methods of the intervention group (or vice versa) and tries to train, they will be classified as contaminated participants.

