Secondly, regarding adverse reactions during the EEG data collection process, if participants show physiological rejection responses or adverse emotions, researchers will immediately cease EEG data collection. Whether to continue the experiment will depend on ensuring the participants' health and safety, as well as their own willingness to either continue participating in the experiment or withdraw, with researchers recording the reasons. Subsequent follow-ups and interventions in this study will be communicated to participants after collective discussion among the research team before any decisions are made.

1. ***Ethical considerations. [This includes the selection of an ethics committee, approval procedures, informed consent process, registration time, and registration authority (please provide registration number after completion)]***

(1) Selection of the Ethics Committee: This trial has selected the ethics committee of the implementing institution, namely the Medical Ethics Committee of Kunming University of Science and Technology.

(2) Approval Process: Before the study begins, the research project proposal and related materials have been submitted for approval in accordance with the procedural requirements of the selected ethics review committee of the research institution.

(3) Informed Consent Process: Before the study begins, researchers will provide paper copies of the informed consent form to the participants and authorized agents, and address any questions related to the informed consent form to ensure that participants and authorized agents understand the content before signing the informed consent form.

(4) Registration Time: March 2024.

(5) Registration Institution: China Clinical Trial Registration Center.

1. ***Participant recruitment. [This includes the selection of recruitment locations, recruitment methods, the screening process, and the researchers conducting the screening]***
2. Recruitment Location: Chenggong Campus, Kunming Medical University.
3. Recruitment Method: This trial will use a combination of online and offline methods to recruit participants:

Offline: Conduct presentations in classrooms, create posters, and distribute flyers;

Online: Use campus platforms such as QQ Space, WeChat Moments, and the school's community bulletin board.

1. Screening Process: Participants will be selected based on their order of participation according to inclusion and exclusion criteria.

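### The rules after an adverse event differ in scope (intervention, research, experiment), and none keeps a participant whose training stops in the T0 to T5 assessments that the ITT analysis needs

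*Protocol*

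**What the plan says.** Three places in the protocol deal with what follows an adverse event.

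- **Definition of Participant Effectiveness Determination, (5) Participant Termination.** The trigger is broad: "any adverse events will constitute a termination condition". The consequence is narrower: "Researchers will discuss such situations with the affected participants to consider premature termination of their intervention". What may end is the intervention.
- **Adverse-event section, weekly questionnaire.** When a participant reports an event, the medical school, the psychology department and the participant confer, and "they will decide whether the subjects experiencing adverse events can participate in subsequent research". What may end is the research. On who is monitored, the section says: "The experimental group will conduct weekly monitoring".
- **Adverse-event section, reactions during EEG recording.** Recording stops. What happens next depends on the participant's health and safety and on "their own willingness to either continue participating in the experiment or withdraw, with researchers recording the reasons". What may end is the experiment. The following sentence leaves later follow-ups and interventions to discussion within the team.

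Two other provisions bear on this. Item (1) of the participant definitions says: "Participants who withdraw voluntarily will not be included in the analysis". Statistical analysis methods promises both an ITT and a PP analysis. Table 1 schedules the primary and secondary outcomes at T0 to T5, that is, from post-intervention to one year. No section states whether a person whose training has stopped keeps attending those visits.

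**The concern.** Stopping training and ending outcome assessment are different events, and an ITT analysis depends on keeping them apart. If the adverse-event decision can take a person out of the research, the later outcomes are not collected. An analysis plan can model missing data but cannot recover them. This is therefore a matter of trial conduct for the protocol to settle, not a detail to leave to the SAP.

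The loss is also unlikely to be random. The mental and cognitive events that the protocol lists (anxiety, depression, disorganized thinking, forgetfulness) overlap with what the trial measures: DASS-21 is a secondary outcome and executive function is the target. The listed harms are those of meditation, and the weekly monitoring that triggers the decision is described for the experimental group only. If poor responders leave mainly from that arm, it may appear better than it is. Measurement would also end for the people whose course after an event matters most for safety.

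**Working it through.** **1. The provisions side by side**

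| Place in protocol | What the decision concerns | Are T0 to T5 assessments kept? |
|---|---|---|
| Participant Termination, item (5) | the intervention | not stated |
| Adverse-event section, weekly questionnaire | subsequent research | not stated; can end |
| Adverse-event section, EEG reactions | the experiment; follow-ups left to team discussion | not stated; left open |

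One event can fall under the first two rows at once, with different consequences. Training lasts one week, so a removal during it would cost T0 and the five later visits, leaving only the two baseline measurements. A participant who chooses to withdraw also falls under item (1) and leaves the analysis altogether. Whether a removal agreed among the three parties counts as voluntary is not said.

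**2. The protocol's own figures, used here only for scale**

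Sample size estimation gives a target of 125 ms and an SD of 250 ms, so d = 125 / 250 = 0.5. A paired two-sided t-test at 0.05 with power 0.80 needs n = 34 (power 0.808 at 34 and 0.795 at 33), as stated. The 41 for the experimental group is 34 x 1.2 = 40.8, rounded up.

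**3. Formula for the bias**

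Let p be the share of an arm removed from measurement, and g the amount by which those kept do better than those removed.

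- Mean of the full arm = (1 - p) x mean of kept + p x mean of removed.
- Mean of kept - mean of full arm = p x g.
- Bias in the comparison = (p x g) in the mindfulness arm - (p x g) in the control arm.

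Here p is the share removed, not the share with an adverse event.

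**4. Numbers**

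The documents give neither p nor g. Assumed: p = 5-15% of the 41 IGD participants in the mindfulness arm (41 x 0.05 = 2.05 and 41 x 0.15 = 6.15, about 2 to 6 people), g from 0 to 1 SD, and no removals in the control arm.

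| p | g = 0 | g = 0.5 SD (125 ms) | g = 1 SD (250 ms) |
|---|---|---|---|
| 5% | 0 | 6.25 ms (5% of 125) | 12.5 ms (10%) |
| 10% | 0 | 12.5 ms (10%) | 25 ms (20%) |
| 15% | 0 | 18.75 ms (15%) | 37.5 ms (30%) |

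A negative gap reverses the sign: with g = -62.5 ms, p = 5% gives -3.1 ms and p = 15% gives -9.4 ms. If p x g is the same in both arms, the bias in the comparison is zero. If everyone is measured after training stops, p = 0 and this bias disappears.

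**The case against.** The strongest reply is that no provision requires removal. Participant Termination asks researchers only to consider ending the intervention. The weekly-questionnaire decision is made case by case, with the participant as one of three parties. The EEG paragraph gives weight to the participant's own willingness, has reasons recorded, and names follow-ups and interventions separately. All of this stands. A reader might infer that everyone with an adverse event is dropped, or that the protocol treats stopping training and leaving the study as one event throughout. The text supports neither.

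A reader might also infer that the mindfulness arm will look better by a known amount. The documents do not support that either. Outcome Measures has researchers ask participants about adverse reactions daily during the intervention, without limiting this to one arm, and Participant Termination applies to all, so zero control removals is an extreme case. The monitoring sentence may even mean that the study team does the monitoring, although the randomization section uses the same term for the breath meditation arm. Some listed events, such as bodily tension, pain and gastrointestinal complaints, give no evident reason for slower Stroop responses, so the gap could be near zero.

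Finally, a rule that only the participant's refusal may end follow-up would override the health-and-safety judgement that the adverse-event section already contains. That objection is sound, and no such rule is proposed.

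What remains is that the three scopes differ, one of them reaches the research as a whole, and no text keeps assessment going once training stops.

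**Conclusion.** The point holds as an inconsistency of scope with a consequence for the analysis. Followed as written, the weekly-questionnaire rule can end outcome collection after an adverse event. Together with the exclusion of voluntary withdrawals, this would leave the ITT analysis without those people's data. The result may be biased, possibly towards the mindfulness arm.

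The sign is an inference from the overlap between listed harms and outcomes and from the one-arm description of weekly monitoring. The range of 0 to about 38 ms (up to 30% of the target) illustrates scale only. It rests on an assumed share removed, an assumed gap, no control removals, and an analysis of observed outcomes only. The change should be made before enrolment, and the protocol says that the trial has not started.

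**What to change.** Reconcile Participant Termination with the two paragraphs of the adverse-event section so that stopping training and ending outcome assessment are separate decisions, worded alike for both arms. State that after training stops the scheduled T0 to T5 assessments continue, with the participant's consent and subject to the health-and-safety judgement already in the protocol, and that these data enter the ITT analysis. Align item (1) on withdrawal with that statement. Record stopped training and left follow-up as two separate events, each with date and reason.

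The cost is some protocol wording, one added form field and a few more follow-up visits for people already enrolled. When training or an EEG recording should stop is a clinical matter and is not addressed here.
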